# Implementation and scale-up of a single-visit, screen-and-treat approach with thermal ablation for sustainable cervical cancer prevention services: a protocol for a stepped-wedge cluster randomized trial in Kenya

**DOI:** 10.1186/s13012-023-01282-3

**Published:** 2023-06-26

**Keywords:** Human papilloma virus, Cervical cancer, Thermal ablation, Single visit, Screen-and-treat approach, Kenya, RE-AIM, CFIR, ORIC, Implementation science

## Abstract

**Background:**

An important cervical cancer prevention strategy in low- and middle-income countries (LMICs) has been single-visit screen-and-treat (SV-SAT) approach, using visual inspection with acetic acid (VIA) and ablative treatment with cryotherapy to manage precancerous lesions. While SV-SAT with VIA and cryotherapy have established efficacy, its population level coverage and impact on reducing cervical cancer burden remains low. In Kenya, the estimated cervical cancer screening uptake among women aged 30–49 is 16% and up to 70% of screen-positive women do not receive treatment. Thermal ablation for treatment of precancerous lesions of the cervix is recommended by the World Health Organization and has the potential to overcome logistical challenges associated with cryotherapy and facilitate implementation of SV-SAT approach and increase treatment rates of screen-positive women. In this 5-year prospective, stepped-wedge randomized trial, we plan to implement and evaluate the SV-SAT approach using VIA and thermal ablation in ten reproductive health clinics in central Kenya.

**Methods:**

The study aims to develop and evaluate implementation strategies to inform the national scale-up of SV-SAT approach with VIA and thermal ablation through three aims: (1) develop locally tailored implementation strategies using multi-level participatory method with key stakeholders (patient, provider, system-level), (2) implement SV-SAT approach with VIA and thermal ablation and evaluate clinical and implementation outcomes, and (3) assess the budget impact of SV-SAT approach with VIA and thermal ablation compared to single-visit, screen-and-treat method using cryotherapy.

**Discussion:**

Our findings will inform national scale-up of the SV-SAT approach with VIA and thermal ablation. We anticipate that this intervention, along with tailored implementation strategies will enhance the adoption and sustainability of cervical cancer screening and treatment compared to the standard of care using cryotherapy.

**Trial registration:**

NCT05472311.

Contributions to the literature
Application of an evidence-based, contextually appropriate, and replicable implementation strategy to improve screening and treatment of precancerous lesions of the cervix in low- and middle-income country settings.Rigorous evidence of impact on screening and treatment uptake using the single-visit and screen-and-treat approach with VIA and thermal ablation.Generate data on budget impact of the strategy to support scale up and sustainability planning.

## Background

Cervical cancer is almost entirely preventable with current technologies, yet it remains the fourth most common cause of cancer incidence and mortality among women globally [1]. Ninety percent of cervical cancer cases and deaths occur in low- and middle- income countries (LMICs) [2]. In response to this public health problem, the World Health Organization (WHO) issued a call in 2018 to eliminate cervical cancer globally [3]. In Kenya, cervical cancer is the second most prevalent cancer and the most common cause of cancer death in women, with an age standardized incidence of 33.8/100,000, resulting in 5236 cases and 3211 deaths in 2020 [4]. Despite the well-documented need for cervical cancer prevention, just 16% of Kenyan women (age 30–49) were screened in 2015 [5], far below the WHO’s target of 70% by 2030 [6]. For this reason, the Kenya National Cancer Control Strategy 2017–2022 prioritizes early detection strategies for cervical cancer [7].

The current WHO guideline recommends women over 30 years old be screened for cervical cancer every 3 years via visual inspection with acetic acid (VIA), Lugol’s iodine, or cytology when human papillomavirus (HPV) testing is not available as a primary screening modality [8]. The single-visit, screen-and-treat approach (SV-SAT) with VIA to detect and manage precancerous or cancerous lesions has been recommended for cervical cancer prevention in LMICs like Kenya because of its low cost and facilitation of treatment uptake among screen-positive women compared to cytology or HPV testing [9, 10]. VIA has demonstrated effectiveness in detecting cervical cancer at the population level in LMICs such as Zimbabwe [11–13]. However, implementation and maintenance cervical cancer screening programs in Kenya has been suboptimal due to multi-level barriers [14]. At the individual/patient level, low population-level awareness of screening services has impeded the uptake [15]. Other studies have also reported structural barriers such as attrition of trained personnel and supply and equipment stockouts [15, 16].

In the SV-SAT approach, women who screen positive for precancerous lesions are immediately treated with ablative therapy such as cryotherapy or thermal ablation, which minimizes loss to follow-up or attrition of screen-positive women [17, 18]. According to the 2015 Kenya STEPwise survey report on non-communicable diseases [5], up to 70% of screen-positive women do not receive treatment [19]. Low fidelity of the SV-SAT approach and treatment with cryotherapy in Kenya has been attributed to programmatic and logistical challenges of implementing cryotherapy in low-resource settings [15]. For example, large tanks of compressed refrigerant gas are difficult to supply and transport consistently to remote areas [14, 15, 20]. The equipment (cryotherapy probe and gas) is costly, and clinics that maintain cryotherapy equipment in Kenya have reported challenges with equipment failure and high turnover of trained personnel [21]. The 2019 WHO recommendations have added thermal ablation as another ablative treatment method for precancerous lesions [22]. The portable thermal ablation device can be charged with electricity, batteries, or solar panels, which is ideal for low-resource settings [23]. While the safety, efficacy, and acceptability of thermal ablation to women has been demonstrated in limited settings in parts of Zambia and Kenya [20, 24, 25], the drivers of its implementation and scale-up have not been determined.

Implementation strategies of evidence-based interventions (EBIs) such as SV-SAT with VIA and thermal ablation can facilitate identification of multi-level determinants of cervical cancer screening and treatment uptake and tailor EBIs to the local contexts to enhance their adoption and sustainment. We hypothesize that this intervention, along with tailored implementation strategies, will enhance the adoption and sustainability of cervical cancer screening and treatment compared to the standard of care using cryotherapy. Our specific aims are to:

Aim 1) Develop locally tailored implementation strategies using multi-level participatory method with key stakeholders (patient, provider, system-level)Aim 2) Implement the intervention and evaluate clinical and implementation outcomes using the RE-AIM framework.Aim 3) Assess the budget impact of the intervention compared to single-visit, screen-and-treat method using cryotherapy.

We anticipate that the findings from this project will inform wider implementation and scale-up SV-SAT approach with VIA and thermal ablation and provide critical evidence to guide national policy and serve as a model for cervical cancer prevention efforts in similar LMIC settings. (NCT05472311).

## Methods

### Study design

This 5-year prospective, stepped-wedge, cluster randomized trial (hereafter referred to as “TIBA,” and translating to *cure/treatment* in Kiswahili, the Kenyan national language) aims to develop and evaluate implementation strategies to inform the national scale-up of SV-SAT approach with VIA and thermal ablation. We will initially use qualitative research with a participatory approach to develop an implementation strategy to introduce the intervention (SV-SAT with VIA and thermal ablation) in ten reproductive health clinics in central Kenya. Subsequently, we will evaluate the implementation of the intervention following the stepped-wedge cluster randomized trial design. The conceptual framework for this trial was informed by the implementation research logic model (IRLM, Fig. 1). The IRLM has been described extensively in the literature, but briefly, involves identifying and specifying the relationship between the determinants, implementation strategies, mechanism of action, and outcomes of evidence-based interventions [26]. A mixed-methods evaluation will assess implementation success. The Reach, Effectiveness, Adoption, Implementation and Maintenance (RE-AIM) framework will be used to assess the impact, which has demonstrated capacity to guide assessments of the public health impacts of complex intervention by capturing formative, process and outcome dimensions on the individual, organizational, and policy levels [27]. We will also use the Consolidated Framework for Implementation Research (CFIR) to guide the data collection and interpretation of the implementation outcomes and determine necessary adaptations in delivery as well as organizational determinants of successful implementation [28]. The CFIR is a meta-framework that incorporates components from evidence-based implementation process theories, guides intervention planning and implementation, and identifies contextual influences that explain the heterogeneity of implementation success across settings. This meta-framework is organized into five domains, comprised of 39 constructs and serves as a guide to identify core and adaptable components, an essential requirement to support scaling of interventions and has been applied successfully in LMICs settings [29]. The use of these established implementation science frameworks will help ensure our evaluation provides actionable, appropriate, and holistic implementation guidance to scale SV-SAT with VIA and thermal ablation across heterogeneous health facilities. As part of this comprehensive evaluation, we will also assess the cost and budget impact of the intervention, which is critical for policymakers in LMICs to define priorities and actualize realistic and effective planning. Our project will produce a comprehensive delivery guide in collaboration with the Kenya National Cancer Control Program (NCCP) along with implementation guidelines for scaling nationwide. The CONSORT extension for stepped-wedge randomized trials and the Standards for Reporting Implementation Studies (StaRI) Statement are available in additional materials [30].

**Fig. 1 Fig1:**
[figure not shown]
Conceptual model of the TIBA trial

### Setting

We will implement this work in ten health facilities in Embu, Kiambu, Nairobi, and Murang’a counties in central Kenya, including urban faith-based, rural, and urban health facilities. The sample is purposively selected to be nationally representative and heterogeneous in order to provide contextually relevant guidance applicable for national scaling of the intervention. The eligibility to participate will include the following: (1) Hospital levels 3–5 according to the Kenyan level system, public or private medical facilities; (2) current use of VIA as the primary screening method; and (3) cervical cancer screening volume over a 4-month period (greater than 1000) [31]. Additional factors such as geographical setting (urban vs. rural), leadership/management structure, funding mechanism (public vs. private/charity), number of providers trained in cervical cancer screening and their scope of practice, and patient fee structure for screening as well as screening volume will be considered. Site level variation is critical to scale the intervention in heterogeneous clinics with different management and staffing systems.

### Randomization

Three to four clinics will be randomly assigned to one of three 6-month implementation waves at the stakeholder meeting at the conclusion of year 1. The clinics will be stratified by size.

### Aim 1: develop locally tailored implementation strategies using multi-level participatory method with key stakeholders (patient, provider, system-level)

The intervention will include cervical cancer screening and treatment using SV-SAT with VIA and thermal ablation. To build on existing data from the region and the investigative team, we will use participatory methods to conduct qualitative interviews with clients, front-line health providers, facility managers, and policy makers in the Ministry of Health to assess and address barriers and facilitators to uptake and provide information on the introduction of the intervention through stakeholder engagement. Based on informal engagement with frontline health care workers and managers in the study area, we anticipate openness to the intervention. Existing barriers will be identified early in project implementation to address any unforeseen challenges to implementation. At the end of year 1, we will hold a stakeholder workshop to map out context-specific strategies that address potential barriers to intervention uptake and account for heterogeneity in provider and system inputs across facilities. Information gathered during these research activities will help investigators refine the essential components of the implementation strategy to be evaluated in Aim 2.

#### In-depth qualitative interviews

In-depth interviews will use semi-structured topic guides, to explore barriers and facilitators to potential adoption, delivery, and sustainment of the intervention. We will also interview frontline health providers carrying out cervical cancer screening in reproductive health clinics (*n* = 20). These health providers will be purposively sampled by profession to ensure representation of nurses, clinical officers, and doctors who provide reproductive health care, as well as a subset with management roles (*n* = 10), and two female patients recently screened for cervical cancer in each potential study facility (*n* = 20). Sample size determination in qualitative research rests on maximizing potential for saturation (when new interviews do not meaningfully add to codes and themes already represented in the previously collected data). Based on experience, we fully envision reaching saturation with (*n* = 5) policymakers stationed at the National Cancer Institute and the Division of Reproductive Health at the Ministry of Health of Kenya. Our investigative team has extensive experience conducting in-depth interviews with health providers.

#### Qualitative data analysis

Digital recordings of the interviews will be transcribed. We will then use a deductive framework method with a combination of deductive and inductive analysis to allow for exploration of specific themes but also allow space to discover other unexpected aspects of participants’ experiences. We will use the qualitative data management computer program Dedoose, which will then be repeatedly sorted and re-reviewed by two experienced social scientists to identify a broader set of concepts [32].

#### Stakeholder workshop

To complement these interviews, we will conduct a 1-day stakeholder workshop, in collaboration with the National Cancer Institute to present findings from the qualitative work and introduce our study, specifically the phased introduction of intervention and the proposed implementation strategy development and refinement process. We anticipate the meeting size will be approximately 40–50 people. Invitees will include representation from the National Cancer Institute, Ministry of Health leadership, county-level reproductive health coordinators, and health facility managers and select front line health providers from participating reproductive health facilities that provide VIA or are interested in doing so. At this workshop, we will engage stakeholders in mapping exercises to identify how services for cervical cancer screening and treatment are currently provided across each site. The results of the mapping and the qualitative findings will be reviewed to identify categories of determinants driving implementation at the facility level. Baseline conceptual framing of the implementation process will be introduced using IRLM so facility level teams can conceptually link determinants, their implementation strategies, and the hypothesized mechanisms of action to implementation and clinical outcomes. Throughout the stakeholder meeting process, we will invite stakeholders to suggest preconditions and/or adaptations to the planned implementation of the intervention that may be necessary in specific local contexts and settings, and we will attempt to incorporate ways to include these implementation guidelines for the sustainable introduction of the intervention. Specifically, we will use this feedback to refine our design to be compatible with facility workflow and systems, aligns with organizational culture, and is agreeable to our stakeholders. Finally, at this workshop, we will collectively randomize clinics into one of three phases to begin implementation. The randomization will be performed in a public manner in order to ensure organizational receptivity and to build ownership of the implementation process.

#### Data collection and abstraction

The data on facility-level infrastructure including availability of equipment, supplies, and current staffing (numbers, cadre and training) and patient flow will be obtained. Infrastructure supplies and staffing data collection will be collected at three time points in the ten RH study facilities; before and after each implementation wave and at the end of the maintenance phase. Routine data on the proportion of women screened, screened positive, and treated for abnormal lesions will be abstracted monthly, by research staff, covering a minimum period of 6 months prior to introduction of the intervention at any facilities and continuing through the end of the maintenance phase. During pre-implementation periods, clinics will contribute data to the “control” condition in the stepped wedged trial.

### Aim 2: implement the intervention and evaluate clinical and implementation outcomes using the RE-AIM framework

#### Overview

At 10 reproductive health clinics in central Kenya, we will introduce the intervention and site-specific implementation strategy developed in Aim 1 in a stepped-wedge fashion and rigorously evaluate how effectively this strategy is disseminated and implemented. In three successive 6-month waves, we will roll out the intervention at three to four clinics. A maintenance phase of varying lengths will be conducted across all waves.

#### Power and sample size

The stepped-wedge study design is powered based on the primary effectiveness outcome, which is the proportion of screen-positive women who receive same-day treatment. According to data on cervical cancer screening and preventive treatment for Kiambu county from 2017 to 2019, 20% of cervical cancer screening clients who screened positive received cryotherapy or LEEP. Routine data from our proposed study facilities show an average of 30 clients per month screened at each facility in the first 3 months of 2020. Assuming 6-month waves, 30 clients screened per month and a 5% screen positive rate, we expect an average of 9 screen-positive women per facility per wave. Assuming an intracluster correlation coefficient of 0.2, alpha = 0.05, and 20% treatment coverage pre-intervention, we will have 80% power to detect a three-fold increase to 60% treatment coverage with the intervention (R [v 3.6.3] package swCRTDesign [v 3.1]). We estimate that 90% of screen-positive women will be eligible for ablative treatment.

#### Training

Before the implementation of the intervention, we will train health providers in participating reproductive health clinics, with a refresher course on VIA and thermal ablation treatment techniques as part of single visit as per IARC guidelines. The training curriculum will be adapted to address gaps identified in year 1. On-site hands-on training will be done at each facility with support of research training team for a duration of 4 days. Outreach community activities will be done prior to scheduled on-site training to provide an adequate number of clients for screening and demonstration of thermal ablation. Each trained provider will be required to complete a set number of procedures before they receive a proficiency certificate. The selected reproductive health clinics have some of their providers trained on VIA and cryotherapy. Our team of investigators has three reproductive health experts with thermal ablation training skills who will develop and train a team of trainer of trainers at each reproductive health clinic. Regular training at each clinic will be provided with engagement of a Kenyan consultant gynecologist to provide consultant training services for the trainer of trainers for the initial 2 clinics. Thereafter, the research team and the county trainer of trainers will provide on-site hands-on training. Training will be led by specialists skilled in colposcopy, loop electrosurgical excision procedure (LEEP), cryotherapy, and thermal ablation. Quarterly CME and refresher training during implementation will be done. In addition to thermal ablation training, CME-type training on cervical cancer prevention interventions and refresher didactic training on VIA will be performed.

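### Women treated during pre-crossover thermal-ablation training are not separated from the control data, and at 9 screen-positives per clinic-wave a few of them move the primary effect.

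*Protocol article*

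**What the plan says.** The protocol article's Training section fixes the order of events: "Before the implementation of the intervention, we will train health providers in participating reproductive health clinics". Training takes place at the clinics: "On-site hands-on training will be done at each facility with support of research training team for a duration of 4 days". Clients are brought in for it by community outreach run beforehand, "to provide an adequate number of clients for screening and demonstration of thermal ablation". There is also a certification rule: "Each trained provider will be required to complete a set number of procedures before they receive a proficiency certificate". The type of procedure and the deadline for completing it are not stated.

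The section on data collection and abstraction describes the source of the outcome data: "Routine data on the proportion of women screened, screened positive, and treated for abnormal lesions will be abstracted monthly, by research staff". It then gives the allocation rule: "During pre-implementation periods, clinics will contribute data to the “control” condition in the stepped wedged trial".

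Under Power and sample size, the primary outcome is same-day treatment among screen-positive women. Under Effectiveness, treatment by thermal ablation, cryotherapy, LEEP or any other procedure counts. Under Data analysis, individual women are compared before and after the intervention. The article describes no transition period and no separate handling of training clients.

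**The concern.** Women found through training outreach and ablated under a trainer are treated because a demonstration needs cases. Their treatment says little about whether the clinic's routine service treats screen-positive women, either with its existing methods or after the roll-out. Yet the stated sequence places them before implementation, and the stated rule makes that period control. They would then count as treated controls in the last control period of each clinic, next to crossover. If someone later decides that training marks the start, the same women become early intervention successes.

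The direction of the error therefore depends on a dating choice that the article leaves open. Because the protocol expects few screen-positive women per clinic-wave, a handful is enough to matter. Outreach screening would also add to the monthly counts of women screened and screen-positive, which are secondary outcomes.

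**Working it through.** **Inputs from the protocol.** 10 clinics in three 6-month waves of three to four; 30 screened per month; 5% positive; ICC 0.2; alpha 0.05 (taken as two-sided); 20% versus 60%. Six months of baseline plus 6 months of intervention and 18, 12 or 6 months of maintenance make five 6-month periods.

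**Assumptions.** k training cases per clinic (k = 1, 2, 3, 5), all treated the same day; clinics split 3-3-4; fixed period effects.

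**The plan's own figures.**
- Cell size: 30 × 6 × 0.05 = 9 screen-positive women, as stated.
- Residual variance at the mean of 20% and 60%: 0.4 × 0.6 = 0.24. Between-cluster variance: 0.24 × 0.2/0.8 = 0.06.
- Independent facility-by-wave effects: cell variance 0.06 + 0.24/9 = 0.087. Generalised least squares gives SE 0.139 and power Φ(0.40/0.139 − 1.96) = 82%; with a 3-4-3 split it is 79.5%. This variant comes near the stated 80%.
- Facility intercept only: SE 0.091 with five periods, power about 99%.

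The Data analysis section names random intercepts for facility and wave without fixing this structure, so both variants are shown.

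**Shift in the affected cell.** Counted as control, the last control cell becomes (0.2 × 9 + k)/(9 + k). Counted as intervention, the first intervention cell becomes (0.6 × 9 + k)/(9 + k).

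**Effect on the estimate.** With the planned weights (9 per cell), a common shift in that cell moves the estimate by 0.735 times the shift under independent facility-by-wave effects. Under a facility intercept with five periods the multiplier is 1.02. For k = 3 as control, the cell goes from 0.20 to 4.8/12 = 0.40, so the estimate is 0.40 − 0.735 × 0.20 = 0.25, or 0.40 − 1.02 × 0.20 = 0.20.

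| k | Last control cell | Estimate, facility-by-wave | Estimate, facility intercept | First intervention cell | Estimate, facility-by-wave | Estimate, facility intercept |
|---|---|---|---|---|---|---|
| 0 | 0.20 | 0.40 | 0.40 | 0.60 | 0.40 | 0.40 |
| 1 | 0.28 | 0.34 | 0.32 | 0.64 | 0.43 | 0.44 |
| 2 | 0.35 | 0.29 | 0.25 | 0.67 | 0.45 | 0.47 |
| 3 | 0.40 | 0.25 | 0.20 | 0.70 | 0.47 | 0.50 |
| 5 | 0.49 | 0.19 | 0.11 | 0.74 | 0.51 | 0.55 |

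In the facility-by-wave variant, counting the women as control lowers power from 82% to about 69%, 56%, 45% and 28% for k = 1, 2, 3 and 5.

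**Sensitivity.**
- If 90% of training cases are treated (the protocol's expected eligibility for ablation), k = 3 as control gives a cell of (1.8 + 2.7)/12 = 0.375 and estimates of 0.27 or 0.22.
- The Setting section requires more than 1000 screened in 4 months. That is 250 per month, and 250 × 6 × 0.05 = 75 screen-positives per wave. With k = 3 the last control cell is (15 + 3)/78 = 0.23 and the estimate 0.36 to 0.38. Counted as intervention, the estimate is 0.41 to 0.42.
- At 5% positive, k = 3 needs 3/0.05 = 60 outreach screens, a third of the 180 expected per clinic-wave. k = 5 needs 100.

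**The case against.** The strongest reply is that the two sections do not contradict each other. Exact crossover dating and exclusion of training clients could sit in a full protocol or analysis plan that is not shown. That would answer a complaint about missing detail. It does not fully answer this one, because the article itself fixes a rule for pre-implementation data and schedules the study procedure inside that period.

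Several further points stand and limit the claim:
- A reader might infer that every pre-implementation record, training included, is declared control. The text does not say so. It speaks of routine data, which could be read to leave demonstration clients out, and on-site training could itself be seen as the introduction of the intervention.
- A reader might infer that each provider must perform a set number of thermal ablations before crossover. The text says only procedures, in training that also covers VIA, and gives no deadline.
- A reader might call the intervention branch plain bias. Table 3 lists training under start-up costs and community outreach under implementation costs, so counting women reached this way is partly a choice of estimand.
- The number of cases is unknown. Five per clinic would need about 100 outreach screens around a 4-day training, so the lower end of the range is easier to believe.

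**Conclusion.** The concern holds in a limited form. Following the article's stated sequence and rule, same-day treatments generated by training fall into the last control period and lower the estimated effect. Dating crossover at training moves them to the first intervention period and raises it. The documents do not show which will happen, and they do not establish that the primary result will be badly wrong.

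The size rests on three things the article does not settle: the number of training cases, the random-effects structure, and the screening volume. At 9 screen-positives per clinic-wave, 1 to 3 treated training cases per clinic cost about 0.06 to 0.20 of a true 0.40 effect if counted as control, or add about 0.03 to 0.10 if counted as intervention. Five cases per clinic under the facility-intercept model give the most extreme figure, 0.11, which should not be taken as the expected result. If the eligibility volume is the true one, the distortion from three cases is 0.04 or less. The remedy is cheap enough to be worthwhile across this range.

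**What to change.** State each clinic's crossover date relative to its on-site training. Add a flag to the abstraction form for women recruited or screened for training. In the primary analysis, leave out of both conditions the window from the start of training outreach to the end of the 4-day on-site training. Report a sensitivity analysis that includes those women, and give their number per clinic. Apply the same window to the counts of women screened and screen-positive.

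The cost is one field on the form, one or two sentences in the analysis section, and a few days of data per clinic. How training is delivered need not change.
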